### Follow-up

A formal assessment of disease response will be made 6 months post-randomisation (or at least 2 months after last treatment if treatment has been delayed). As shown in Figs. 2 and 3, this will require a physical examination and local laboratory tests; the collection of blood, bone marrow aspirate and trephine samples (for participants randomised to treatment, and trephine only where clinically indicated); CT scan (where clinically indicated); and assessment of QoL.

Follow-up visits to assess ongoing disease response and survival will be made every 3 months between 9 and 36 months post-randomisation. Participants who are MRD-negative post-consolidation treatment will also have blood collected at 12, 24, 36 and 48 months post-randomisation. All participants will be followed annually for survival until death. MRD blood assessments will end once a participant becomes MRD-positive.

All trial MRD testing will be carried out centrally by the Haematological Malignancy Diagnostic Service at Leeds Teaching Hospitals National Health Service (NHS) Trust using the harmonised European Research Initiative on CLL method [14] to ensure standardisation of reporting. Participants who are MRD-negative at baseline will have blood collected for MRD analysis at 12, 24 and 36 months post-registration. No further samples are collected if the participant becomes MRD-positive.

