### Trial population

Patients who are eligible for the trial must be at least 18 years old, have previous confirmation of CLL, have undergone between one and three regimens of chemotherapy previously ending between 3 and 24 months before enrolment, have a peripheral B-cell count of <5 × 10^9^/L, have a response to the most recent chemotherapy treatment for CLL with PR, complete remission with incomplete marrow recovery (CRi) or CR. The patient must also be capable of giving written consent and have a World Health Organisation (WHO) performance status of 0 or 1.

Patients with any of the following characteristics are excluded from the trial: disease progression after response to last therapy, active infection, previous anaphylaxis to monoclonal antibodies, previous treatment with obinutuzumab, central nervous system involvement in CLL, mantle cell lymphoma, other severe concurrent diseases or mental disorders that could interfere with their ability to participate in the study (including moderate or worse cardiac diseases), known HIV positivity, positive serology for hepatitis B or C virus, persisting severe pancytopenia (neutrophils <0.5 × 10^9^/L or platelets <50 × 10^9^/L) or transfusion-dependent anaemia, vaccination with a live virus within 28 days, active haemolysis (patients with haemolysis controlled with prednisolone at a dose 10 mg or less per day can be entered into the trial), creatinine and bilirubin less than two times the upper limit of normal, previously treated with an allogeneic stem cell transplant, pregnant or lactating women, or women/men who are capable of conceiving children and who are unwilling to use appropriate medically approved contraception during and for 18 months after receiving treatment.

Once participants provide consent for the trial, peripheral blood will be tested for MRD. Patients who are MRD-negative will not be eligible for randomisation but will still be followed annually for MRD. Patients who are MRD-positive will have bone marrow and trephine samples tested centrally to confirm MRD level in the aspirate, a stratification factor for randomisation. To be randomised, participants must have an MRD-positive peripheral blood sample between 3 and 24 months since completing the last treatment for CLL and be confirmed as MRD-positive in the bone marrow. Participants must also have clinically and radiologically confirmed absence of lymphadenopathy (largest lymph node 1.5 cm or less in minimum diameter).

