### Secondary endpoint analyses

All secondary endpoint analyses comparing randomised participants will be assessed at the same time as the primary endpoint of PFS. The proportion of participants with undetectable MRD will be summarised (with 95% CIs) for participants randomised to consolidation therapy with obinutuzumab at 6 months post-randomisation and then at every time point at which MRD is assessed. CR, CRi and overall response (at least a PR) will be summarised (with 95% CIs) for participants randomised to consolidation therapy with obinutuzumab at 6 months post-randomisation and then at every time point at which response is assessed.

OS and treatment-free survival (TFS) (i.e., time from randomisation to next treatment or death) will both be assessed using Cox proportional hazards models to compare trials arms, adjusting for the minimisation factors. Kaplan-Meier curves, 95% CIs and median survival estimates will also be produced for both analyses by trial arm.

Participants who are registered and eligible but MRD-negative and so not randomised will also be followed for progression and death and will contribute to three secondary endpoint analyses. PFS, OS and duration of MRD negativity (i.e., time from end of most recent therapy for CLL to date of progression or death; date of death; or date of MRD relapse or death, respectively) will be assessed using Cox proportional hazards models to compare those who are MRD-negative at registration with those who become MRD-negative following consolidation therapy with obinutuzumab.

Occurrence and frequency of SUSARs, SARs, SAEs, AEoSI, AEs and treatment-related deaths will be summarised by trial arm and overall. In addition, all events will be summarised by maximum CTCAE grade reported and seriousness criteria, and all serious events will be summarised by Medical Dictionary for Regulatory Activities (MedDRA) System Organ Class, by trial arm and overall.

Mean QoL scores and 95% CIs, adjusted for the baseline score, will be calculated for all domains of the European Organisation for Research and Treatment of Cancer (EORTC) Core Quality of Life Questionnaire (QLQ-C30) and the CLL-specific module (EORTC QLQ-CLL16) for each trial arm and at each assessment time point and overall. Wilcoxon’s rank-sum tests will be used to compare the change in score for the trial arms from baseline to each time point.

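### Duration of MRD negativity is compared by Cox model on detection dates, although the two groups' blood tests fall at different times after the negative test that defines each group

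*Protocol article*

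**What the plan says.** The Secondary endpoint analyses section plans Cox models for PFS, OS and duration of MRD negativity "to compare those who are MRD-negative at registration with those who become MRD-negative following consolidation therapy with obinutuzumab". All three start from the same point. PFS is the "time from end of most recent therapy for CLL to date of progression or death", and duration of MRD negativity runs from that same start to MRD relapse or death. The registrants are outside the randomised comparison: "Patients who are MRD-negative will not be eligible for randomisation but will still be followed annually for MRD" (Trial population).

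The Follow-up section fixes the tests. For registrants: "Participants who are MRD-negative at baseline will have blood collected for MRD analysis at 12, 24 and 36 months post-registration". For the other group: "Participants who are MRD-negative post-consolidation treatment will also have blood collected at 12, 24, 36 and 48 months post-randomisation". The status of consolidated participants comes from an earlier assessment: "A formal assessment of disease response will be made 6 months post-randomisation", or at least two months after the last dose if treatment was delayed. MRD monitoring after that is by blood in both groups, in one central laboratory.

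The article mentions no interval-censoring, delayed entry or landmark for this comparison.

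**The concern.** The two schedules look alike because both carry the labels 12, 24 and 36 months, but they count from different events. A registrant is negative at registration and is not retested for a year. A consolidated participant is negative at month 6 and is retested six months later. MRD relapse has no symptom date, so its recorded date is the date of the blood test that found it. A Cox model on those dates treats a difference in test timing as a difference in hazard.

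The analysis serves the listed objective on PFS and OS in those who are, and those who become, MRD-negative. Readers will use it to judge whether negativity produced by consolidation lasts as long as negativity produced by chemotherapy. A hazard ratio away from 1 that comes only from the calendar could be taken for biology.

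**Working it through.** The article gives no figure for this comparison, so there is none to reproduce. The check asks what the planned model returns when both groups have the same relapse hazard.

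**Step 1. Count tests from the defining negative.** Registrants: 12, 24, 36 months. Consolidated: 12 − 6 = 6, 24 − 6 = 18, 36 − 6 = 30, 48 − 6 = 42 months.

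**Step 2. Grid effect alone, worked for one case.** Assumptions: equal group sizes, constant relapse hazard with a 24-month median, S(t) = 2^(−t/24), no deaths, everyone followed to the last sample, and time counted from the defining negative. Entries are proportions of each group.

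| Month | Group tested | Relapses found | Registrants at risk | Consolidated at risk | Ratio r (cons./reg.) |
|---|---|---|---|---|---|
| 6 | cons. | 0.1591 | 1 | 1 | 1 |
| 12 | reg. | 0.2929 | 1 | 0.8409 | 0.8409 |
| 18 | cons. | 0.2463 | 0.7071 | 0.8409 | 1.1892 |
| 24 | reg. | 0.2071 | 0.7071 | 0.5946 | 0.8409 |
| 30 | cons. | 0.1742 | 0.5 | 0.5946 | 1.1892 |
| 36 | reg. | 0.1464 | 0.5 | 0.4204 | 0.8409 |
| 42 | cons. | 0.1231 | 0 | 0.4204 | – |

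Month 42 contributes nothing to the likelihood because no registrant is still at risk. With Breslow ties the Cox estimate h solves

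Σ over consolidated times d/(1 + r·h) = Σ over registrant times d·r·h/(1 + r·h).

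Consolidated relapses at months 18 and 30 sum to 0.4205. Registrant relapses sum to 0.6464. At h = 0.925:
- left: 0.1591/1.925 + 0.4205/(1 + 1.1892 × 0.925) = 0.0826 + 0.2002 = 0.283
- right: 0.6464 × 0.7778/1.7778 = 0.283

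So the hazard ratio is 0.925 where the truth is 1.

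**Step 3. Other medians.** Simulation with 150,000 per group and Breslow ties gives 1.01, 0.93, 0.90 and 0.87 for medians of 12, 24, 36 and 60 months. Efron ties give about 0.97 falling to about 0.86. Overall: about 0.85 to 1.0.

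**Step 4. Dropping the month-48 sample.** Consolidated participants who are still negative are then censored 30 months after their defining test. They leave the risk set before the registrants' 36-month test, so those relapses no longer count. Registrant relapses become 0.2929 + 0.2071 = 0.5000. At h = 1.175:
- left: 0.1591/2.175 + 0.4205/(1 + 1.1892 × 1.175) = 0.0731 + 0.1754 = 0.249
- right: 0.5000 × 0.9881/1.9881 = 0.249

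The bias reverses, to about 1.18 here and about 1.1 to 1.2 across medians of 1 to 5 years.

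**Step 5. The stated origin.** Assume the gap from last chemotherapy to entry is uniform over the eligible 3 to 24 months. Last obinutuzumab dose: day 78, about 2.6 months, so month-6 negativity comes 6 − 2.6 = 3.4 months later. Equal true hazards, medians 12 to 60 months:

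| Origin for the consolidated group | Stated test times | Matched test times |
|---|---|---|
| End of chemotherapy | 0.67–0.68 | 0.66–0.70 |
| End of obinutuzumab | 1.50–1.69 | 1.81–1.91 |

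Time before the negative test is event-free by construction. Counting it as time at risk moves the ratio more than the test grid does, and matching the test times does not repair it.

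**Step 6. The repair.** With time from the documented negative test and the unequal test times kept, an interval-censored likelihood returns 0.998 to 1.011. With time from end of chemotherapy, interval-censoring alone reaches only about 0.8. With entry at the documented negative test added, it returns 0.97 to 1.03.

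**The case against.** The strongest reply is that the grid effect is small and hidden. On the stated origin, matching the test times changes almost nothing when the origin is end of chemotherapy (0.67–0.68 against 0.66–0.70), and moves the ratio further from 1 when it is end of obinutuzumab. This stands: interval-censoring without a corrected start of time at risk would not rescue the analysis, so the two belong together.

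Precision is also poor. At the design's negativity rates of 15% to 35%, 94 treated participants give about 14 to 33 in the consolidated group. If there were 30 to 100 registrants and 60% had events (both assumed), the standard error of the log hazard ratio lies between √(1/8.4 + 1/18) = 0.42 and √(1/19.8 + 1/60) = 0.26. The 95% interval then spans a factor of about 1.7 to 2.3 each way. A distortion of up to 15% would sit inside that interval. The origin bias would not be so easily lost.

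It can also be said that such detail belongs in the analysis plan, which is not shown. But the article does more than stay silent: it names the Cox model and the origin.

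Three stronger readings are tempting and not supported.
- **PFS is distorted too.** A reader might infer this because the text states three-monthly disease visits only after randomisation: "Follow-up visits to assess ongoing disease response and survival will be made every 3 months between 9 and 36 months post-randomisation". The registrants' progression visits are in Fig. 3, which is not shown; annual follow-up is stated only for MRD. If those visits are annual, equal hazards give 1.31–1.38 with no progression found between visits and 1.10–1.12 with 60% found between visits. If they are three-monthly, the ratio is 0.99–1.00. The bias cannot be asserted from the text.
- **The groups are monitored in different tissues.** The month-6 assessment includes "the collection of blood, bone marrow aspirate and trephine samples (for participants randomised to treatment, and trephine only where clinically indicated"), while registrants qualify by blood. That could affect who counts as negative. It does not affect how relapse is detected, and the article does not say that marrow defines the consolidated group.
- **The extra month-48 sample is the fault.** Adding a later sample to otherwise matched grids changes nothing, and Step 4 shows that removing it here does harm.

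**Conclusion.** The point holds for duration of MRD negativity. Test times offset by six months, analysed by Cox model on detection dates, give a hazard ratio of about 0.85 to 1.0 for consolidated versus registrants when the relapse hazards are identical. The stated origin adds a larger bias: about 0.67 from end of chemotherapy, and about 1.5 to 1.9 from end of obinutuzumab over stated and matched test times. The article does not say which end of therapy applies to the consolidated group.

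These sizes assume constant hazards, medians of 1 to 5 years, no deaths, negativity established at month 6, complete testing, and a uniform 3 to 24 month gap before entry. Delayed treatment would shorten the six-month offset.

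The consequence is limited to one secondary, non-randomised comparison. The randomised PFS analysis is untouched. The repair removes the timing artefacts but does not make the two groups otherwise comparable.

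**What to change.** For duration of MRD negativity in this comparison:

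- Treat MRD relapse as interval-censored between the last negative and first positive blood test, in a proportional-hazards model for interval-censored data. Deaths keep their exact dates.
- Start time at risk at the documented negative test: registration for registrants, the post-consolidation assessment for the other group. Use that test as the origin. If end of therapy is kept as the time scale, use it as delayed entry and state which therapy is meant for the consolidated group.
- Keep the month-48 sample. Do not truncate at month 36 under the Cox model.
- Check the registrants' progression visits in Fig. 3. Apply the same method to progression only if they differ from the three-monthly grid.

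The cost is wording in the analysis plan, slightly more analysis work and less familiar software. No visit or sample is added.

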### Data collection

Data will be collected on paper case report forms and entered into a validated trial database by CTRU. A validation check program will be incorporated into the trial database to verify the data, and discrepancy reports will be generated for resolution by the investigator. Priority validations will be incorporated into the validation programme to ensure that any discrepancies related to participant rights or safety are expedited to sites for resolution. Data will be monitored for quality and completeness by the CTRU. Missing data will be chased until received, confirmed as not available or the trial is at analysis. The CTRU/sponsor will reserve the right to intermittently conduct source data verification exercises on a sample of participants, which will be carried out by staff from the CTRU/sponsor. Source data verification will involve direct access to participant notes at the participating hospital sites and the central collection of copies of consent forms and other relevant investigation reports. Data will be held on a secure server at the University of Leeds, and paper case report forms will be stored in a locked unit, with both being accessible only by authorised trial staff.

### Statistical methods and analysis

Statistical analysis is the responsibility of the CTRU statisticians, and a final statistical analysis plan will be written and signed off before any analysis takes place. The primary endpoint of the phase II analyses will be carried out on participants randomised to obinutuzumab who receive at least 4 weeks of treatment. The phase III analyses will be conducted on the ITT population, where participants will be included according to the treatment to which they were randomised. A per-protocol analysis, where participants will be included according to the treatment they received, will be considered for the phase III primary endpoint of PFS if there are a considerable number of protocol violators. The safety population will consist of all participants according to the treatment to which they were randomised.

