**Fig. 2 Fig2:**
[figure not shown]
Schedule of enrolment, interventions and assessments for participants who are suitable for randomisation. *MRD* Minimal residual disease, *PFS* Progression-free survival. ^1^To be performed after the analysis of peripheral blood and only in participants whose peripheral blood is MRD positive. ^2^ To be performed within 4 weeks of randomisation and before treatment is started. ^3^Only for participants randomised to obinutuzumab and if appropriate clinically. ^4^Only required for participants randomised to treatment with obinutuzumab. ^5^Serum immunoglobulins and electrophoresis only. ^6^Tested Centrally

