### Protecting against bias

This trial cannot be blinded, because the two treatment arms are substantially different. Treating consultants need to be aware of the drugs being administered to be able to treat reactions to treatment accordingly. The trial researchers will use an automated randomisation service incorporating randomisation by minimisation, and analyses will be done on an intention-to-treat (ITT) basis. The trial is administered by the chief and principal investigators and the CTRU in accordance with good clinical practice (GCP) guidelines. The assessment of response in the peripheral blood and the bone marrow for MRD will be centralised in a single laboratory, thereby providing standardisation for all assessments.

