### Intervention

Participants randomised to obinutuzumab consolidation will receive 100 mg of intravenous (IV) obinutuzumab on day 1 and 900 mg on day 2. The remaining course of treatment will be 1000 mg IV on days 8, 15, 22 (weekly), 36, 50, 64 and 78 (2-weekly). Participants randomised to no consolidation therapy will receive no treatment.

Participants will be assessed for their suitability for treatment within 1 week before each obinutuzumab treatment. At minimum, tests will be performed to ensure that dose delays or reductions are implemented and that concomitant medications are administered as per protocol.

Prior to medication, analgesic/antipyretic (equivalent to 1000 mg of paracetamol) will be administered before each treatment. Antihistamine (equivalent to 10 mg of cetirizine) will be administered prior to days 1 and 2 of treatment and for remaining treatments for participants with an infusion-related reaction (IRR) (Common Terminology Criteria for Adverse Events [CTCAE] [13] grade 1 or higher) to the previous infusion. Corticosteroid infusion (equivalent to 100 mg of prednisolone) will be administered for days 1 and 2 and for participants with a grade 3 IRR with the previous infusion or participants with a lymphocyte count >25 × 10^9^/L before treatment. No concomitant cytotoxic agents, radiotherapy or vaccination with live viruses should be given.

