#### Non-haematological toxicity

If hypersensitivity to obinutuzumab occurs (typically occurring after previous exposure to obinutuzumab), the infusion should be stopped and treatment permanently discontinued. Participants with a known immunoglobulin E-mediated hypersensitivity to obinutuzumab should not be treated. Obinutuzumab should not be administered in the presence of a severe infection. Prophylactic therapy aimed at preventing a recurrence of a diagnosed infection should be instituted if clinically indicated. For treatment of tumour lysis syndrome, electrolyte abnormalities should be corrected, renal function and fluid balance monitored and supportive care administered, including dialysis as indicated.

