### Primary endpoint analyses

The phase II primary endpoint of MRD negativity in each stage of the phase II part of the trial will be assessed once 9 and 23 participants have received at least 4 weeks of obinutuzumab treatment and been followed until 6 months post-randomisation. The phase III primary endpoint of PFS will be assessed once 120 events (progressions/deaths) have been observed overall. A formal interim analysis will be carried out when 60 events have been observed overall in order to allow large differences between the trial arms to be reported early (Fig. 4). PFS is defined as the time from randomisation to first documented evidence of progression or death. Participants not having progressed or died or who are lost to follow-up at the time of the phase III analyses will be censored at the last date they were known to be alive and progression-free. For the analysis of primacy, we will use a Cox proportional hazards model [15] to compare the trial arms, adjusting for the minimisation factors, to calculate the HR and corresponding 95% CIs. The *p* value to assess for statistical significance will be compared with 0.047 to account for the formal interim analysis. In addition, median survival estimates with corresponding 95% CIs, as well as Kaplan-Meier curves [16], will be produced by trial arm.

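### The per-protocol PFS analysis is defined by treatment received, so obinutuzumab-arm participants who never start would count as controls and the supportive comparison can be biased

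*Protocol article*

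**What the plan says.** Under Statistical methods and analysis, the article fixes the main phase III population: "The phase III analyses will be conducted on the ITT population, where participants will be included according to the treatment to which they were randomised". Protecting against bias says the same: "analyses will be done on an intention-to-treat (ITT) basis".

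The next sentence of Statistical methods and analysis introduces a second PFS analysis: "A per-protocol analysis, where participants will be included according to the treatment they received, will be considered for the phase III primary endpoint". It is conditional: "if there are a considerable number of protocol violators". No number is attached to that condition. The safety population, described immediately afterwards, is again grouped as randomised. The per-protocol sentence is thus the only one of the three to group participants by what they received.

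Two other statements decide what this means in practice. Intervention says of the comparator: "Participants randomised to no consolidation therapy will receive no treatment". Primary endpoint analyses sets the time origin: "PFS is defined as the time from randomisation to first documented evidence of progression or death".

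**The concern.** A per-protocol analysis normally keeps participants in their randomised arms and leaves out those with major departures from the protocol. The rule stated here regroups participants instead. Against an active comparator, a participant who never starts has received neither treatment. Here, not starting is the control condition, so the rule moves that participant into the control group. Movement the other way is not expected, because Trial organisation and administration says obinutuzumab was provided only for protocol treatment.

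The groups being compared are then partly formed by what happened after randomisation. Anyone in the obinutuzumab arm whose early progression or death comes before the first dose cannot count as treated, so that event is charged to the control group. The same kind of participant randomised to control simply stays there. The result would carry a per-protocol label, and a reader could take it as confirming the ITT result without seeing that randomisation had been given up.

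**Working it through.** **Base case.** No figure in the article attaches to this sentence, so the trial's own design was reproduced first as the setting for the simulations. Inputs from Sample size: median PFS 2 against 3.3 years, two-sided 5%, 80% power, 3 years of recruitment plus 3 years of follow-up, 5% drop-out, 188 participants, 120 events.

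- Hazard ratio under exponential PFS: 2/3.3 = 0.606.
- Power with 120 events (Schoenfeld): Φ(√120 × |ln 0.606|/2 − 1.96) = Φ(0.783) = 78.3%. With the ratio rounded to 0.60, 121 events are needed for 80%.
- Event probability with uniform accrual: 1 − (e^(−3λ) − e^(−6λ))/(3λ). This is 0.780 for λ = ln 2/2 and 0.605 for λ = ln 2/3.3, mean 0.693. Then 120/0.693 gives 174 participants, and 174/0.95 gives 184, against 188 stated.

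The plan's figures are reproduced closely enough to serve as the base.

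**What the article does not give.** The share of non-starters, their prognosis, and the time from randomisation to first dose are not stated. A footnote to Fig. 2 says of one set of assessments "To be performed within 4 weeks of randomisation and before treatment is started", which does not fix the gap. Assumed values: 5%, 10% and 15% non-starters; hazard 0.5, 1, 2 or 3 times that of starters; and, in a separate run, a 4-week gap.

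**Hand check of direction.** Let f be the share of would-be non-starters in both arms and r their hazard relative to starters, with no treatment effect. At the start of follow-up:

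- grouping by treatment received: HR = (1 + f)/(1 − f + 2fr)
- excluding non-starters: HR = 1/(1 − f + fr)

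For f = 0.10 and r = 2 these are 1.1/1.3 = 0.85 and 1/1.1 = 0.91. For r = 1 both are 1. For r = 0.5 the first is 1.1/1.0 = 1.10. When r is above 1 the HR averaged over follow-up is nearer 1, because high-hazard participants leave the risk set early.

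**Simulation.** 188 participants, 1:1, unadjusted Cox model, no true effect, 1,500 trials per cell. Each cell gives the mean HR for treatment-received grouping / exclusion of non-starters:

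| Non-starters | 0.5 × hazard | equal | 2 × | 3 × |
|---|---|---|---|---|
| 5% | 1.07 / 1.03 | 1.00 / 1.00 | 0.94 / 0.97 | 0.92 / 0.96 |
| 10% | 1.15 / 1.08 | 1.00 / 1.00 | 0.89 / 0.94 | 0.85 / 0.91 |
| 15% | 1.19 / 1.10 | 1.00 / 1.00 | 0.84 / 0.90 | 0.78 / 0.86 |

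ITT gave 0.99–1.01 throughout. A second simulation with 4,000 trials per scenario agreed: 0.90 for 10% at twice the hazard and 0.86 for 10% at three times.

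**Events before dosing only.** If just the obinutuzumab-arm participants with an event in the assumed 4-week gap are moved, the HR is 0.94 (3,000 trials). Adding 10% non-starters at twice the hazard gives 0.84.

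**How often the result would favour obinutuzumab.** If the final-analysis level of 0.047 were applied (2.35% in that direction), the treatment-received grouping crosses it in 5–29% of null trials at 2–3 times the hazard and in about 5% for the 4-week gap alone. ITT does so in about 2%.

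**Share due to regrouping rather than exclusion.** On the log scale, for 10% at twice the hazard: ln 0.940/ln 0.893 = 0.062/0.113 = 0.55. About half the distortion would therefore remain under ordinary exclusion.

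**The case against.** A reader might infer that the wording necessarily biases PFS towards obinutuzumab. The article does not support that. The bias needs non-starters to have worse prognosis or early events. It vanishes at equal hazard and reverses if non-starters do better. At equal prognosis and a true HR of 0.606 with 10% non-starters, the treatment-received grouping gives 0.60, while ITT is diluted to 0.64. The article points to reasons of both kinds: "Obinutuzumab should not be administered in the presence of a severe infection", but the Discussion also mentions the burden of travel and of returning to hospital, which is not clearly prognostic.

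The size can be overstated too. Entry already requires performance status 0–1 and excludes active infection, progression after the last therapy and severe pancytopenia. The toxicity sections describe neutropenia as a reason to delay dosing and bar dosing only while a severe infection is present; neither means never starting. With a 2-year median and a 4-week gap, an event before day 1 has probability 1 − exp(−0.347 × 4/52) = 2.6%, or 2–3 of 94. Nothing in the article supports a tripled hazard. No significance threshold is attached to this analysis, and the planned Cox model adjusts for six minimisation factors, which the simulations do not. Violators may also mean eligibility or dosing deviations rather than non-starters.

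Finally, the analysis is optional, and a signed-off analysis plan is promised before any analysis.

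These points limit certainty, size and reach, and they stand. They do not remove the defect. The article states a grouping rule rather than leaving one open, and following that rule moves participants between arms.

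**Conclusion.** The point holds as a mislabelled and badly fixed supportive analysis. The stated rule is as-treated. With a no-treatment comparator and PFS timed from randomisation, it counts obinutuzumab-arm non-starters as controls, and so it can bias the comparison. The direction favouring obinutuzumab is the more plausible one, because events before the first dose can move only that way. It is not established, because the article gives neither the number of non-starters nor their reasons.

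The sizes shown rest on the assumed shares, hazards and 4-week gap, on exponential PFS, and on an unadjusted model. Follow-up in the simulations was also not cut at 120 events; with no effect about 188 × 0.780 = 147 are expected. The crossing rates are a scale for the distortion, not an error rate of the trial. The phase III conclusion rests on ITT and does not change.

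**What to change.** For PFS, delete the clause that includes participants by treatment received, and keep every participant in the randomised arm. Define the per-protocol set as the randomised arms restricted to participants without major protocol violations, list those violations before any analysis, and apply the same eligibility criteria to both arms. State beside the result that excluding non-starters still carries selection bias.

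Two additions are optional. A complier-average estimate that respects randomisation could serve as a supportive analysis of the effect in those who start. If the treatment-received grouping is kept, it should be labelled as-treated and exploratory.

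The cost is one changed sentence and a slightly different supportive analysis. No new data are needed, and the analysis plan that is to be signed off before any analysis is a natural place for it.
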